### Randomization and treatment allocation

T0-completers will be randomly assigned to the experimental or waitlist condition by the principal investigator using central block randomization, with a block size of 4. A priori created randomization schemes will be made using www.sealedenvelope.com. This tool provides random lists that will be combined with the participant IDs to randomly allocate participants to the experimental condition or waitlist control condition with an allocation ratio of 1:1.

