### Study design

A non-blinded pragmatic international randomized controlled trial will be performed to study the effectiveness of Adappt in parents of children with a NDD. Participants will be recruited in France, Germany, Israel, Switzerland, and The Netherlands. However, participants from other countries that are able to understand one of the available languages (French, German, Hebrew, and Dutch) can sign-up for the study and participate if they meet the eligibility criteria.

After recruitment via service providers, parent associations, and social media (see “study procedure below”), interested parents fill in a screening form to check for eligibility. Eligible parents receive an e-mail with a link to the (online) baseline questionnaire (T0) and will then be randomized 1:1 to the experimental condition or waitlist control condition. Those randomized to the experimental condition start using the (unguided) digital intervention after the online baseline. One month after baseline participants will complete the post-measurement (T1). Furthermore, two follow-up measures will be conducted, at 4 months (T2) and 6 months after baseline (T3). Those randomized to the control condition receive the intervention that takes 1 month to complete after T2. The flow of participants and measurements can be found in Figs. 1 and 2.

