### Study procedure

Participants will be recruited in the five countries (France, Germany, Israel, Switzerland, and The Netherlands), via (1) the social media channels of relevant stakeholders involved in the project, (2) associations for parents of children with NDDs, and (3) information leaflets and through health practitioners informing parents about the study in clinical centers for children with NDDs. Interested parents will be forwarded to a website of the study. At the website, the parent(s) will find more information about the study, the participant information letter, the option to ask questions via e-mail and have the option to register for the study. Therefore, participants will be referred to a Qualtrics questionnaire where they can register themselves and give informed consent, following the procedure of Kloos et al. [48]. Participants actively confirm that they (1) have read and understand the study information, (2) had time to consider participation and potential questions have been answered, (3) give consent for participation in the study, (4) know that participation is voluntary and withdrawal of consent can be done any time without giving a reason, and (5) consent to the use of their research data as described in the participant information letter.

Participants who give consent will be directed to the screening questionnaire, including questions related to in- and exclusion criteria (i.e., age of the participant, diagnosis, and age of the child with a NDD, being in possession of an e-mail address, smartphone/tablet, and stable internet connection, willingness to use the intervention, the PHQ-9, the GAD-7, and current treatment for a mental health issue). Recruitment will start in September 2024. It is expected that the required number of 212 participants (see “Sample size calculation”) will be reached in January 2025.

Eligible participants will receive a link to the online baseline questionnaire (T0) in Qualtrics, which takes about 30 min to complete. New T0-completers will be randomized once a week to the control or experimental condition and informed via e-mail about the allocation (see “Randomization and treatment allocation”). All participants allocated to the experimental condition will also receive the download instructions and can start using the intervention.

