### Outcome measures

All study measurements will take place online via the online survey program Qualtrics (https://www.qualtrics.com). An overview of the outcome measures and measurement points can be found in Table 2. Measures that were not available for a certain language were translated by native speakers with back-and-forth translation.

**Table 2 Tab2:** Overview of outcome measures and measurement points

Questionnaire	Number of items	Outcome measure	Screening	T0 (baseline)	T1 (Post-intervention)	T2 (follow-up 1)	T3 (follow-up 2)
GSAAS	10	Ability to Adapt		X	X	X	X
MHC-SF	14	Mental well-being	X	X	X	X	X
PSS	10	Parenting stress		X	X	X	X
HADS-A	7	Anxiety symptoms	X	X	X	X	X
PHQ-9	9	Depressive symptoms	X	X	X	X	X
CAPES-DD	24	Parenting self-efficacy and behavior of the child		X	X	X	X
PAC	9	Positive aspects of caregiving		X	X	X	X
SBI	8	Savoring		X	X	X	X
FSCRS-SF	5	Self-reassuring		X	X	X	X
AAQ-II	7	Psychological flexibility		X	X	X	X
CERQ	16	Positive coping skills		X	X	X	X
MAAS	15	Mindfulness		X	X	X	X
Characteristics		Parental and child characteristics	X^d^	X^d^			
CSQ-8		Client satisfaction			EXP		WL

*EXP* Experimental condition, *WL* Waitlist condition

^a^5 weeks after baseline

^b^4 months after baseline

^c^7 months after baseline

^d^The majority of the characteristics are asked at T0; however, those relevant for inclusion are asked in the screenings questionnaire

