### Data handling, management, and storage

The Dutch Personal Data Protection Act will be followed to handle data with confidentiality. Data management will be done following the data management plan (DMP) created for the study via the DMP-tool of the University of Twente, which complies to the policy of national funders and the EU. Personal data (i.e., e-mail addresses) will be collected for the purpose of sending questionnaires via the Qualtrics survey tool, which is ISO 270001 certified [59]. Personal data will be saved separately from the questionnaire data and can be linked to questionnaire data by means of a unique ID-code. Personal data can be accessed by the principal investigator for the purpose of informing participants about the screening for eligibility data and sending the questionnaire invitations. The list with IDs connected to personal data will be stored safely and locked with a password. The coded data will be safely stored for 15 years at the IGS Datalab of the University of Twente, which is ISO 27001 and NEN 7510-certified [75]. The first, second, third, and last author ([name]) of this paper will have access to the final pseudonymized dataset of this trial. Afterwards, pseudonymized data will be archived for long-term storage at Areda, the archiving service of the University of Twente. Participants get access to the self-help app via a personal activation code, this makes the log-data linkable with the study data (i.e., results from questionnaires).

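### The principal investigator applies the pre-made allocation list and can also see who the participants are, so allocation is not concealed from the person who makes it

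*Protocol article*

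**What the plan says.** All references are to the protocol article.

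- **Randomization and treatment allocation.** Parents who have completed T0 are assigned "by the principal investigator using central block randomization, with a block size of 4". On the source of the sequence: "A priori created randomization schemes will be made using www.sealedenvelope.com". On its use, the tool supplies "random lists that will be combined with the participant IDs to randomly allocate participants to the experimental condition or waitlist control condition", in a 1:1 ratio.
- **Study procedure.** Parents register themselves online, consent, and complete an online screening questionnaire and then T0. After that, "New T0-completers will be randomized once a week".
- **Data handling, management, and storage.** "Personal data can be accessed by the principal investigator"; the reasons given are telling parents the screening result and sending out the questionnaires. Personal data, given as e-mail addresses, are kept apart from questionnaire data and can be linked to them by an ID code.
- **Study design.** "A non-blinded pragmatic international randomized controlled trial will be performed". The primary outcome and the mental health outcomes are self-report scales (Outcome measures).
- **Risks and audit.** Neither audits nor a data monitoring committee are planned.

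**The concern.** Concealment means that whoever decides which person takes the next place does not know what that place is. Here one role has both pieces of information when allocation happens: the sequence, because it must be in hand to be joined to the IDs, and the people behind the IDs, because that role corresponds with them about screening and questionnaires.

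This matters more than usual in this trial. Neither parents nor staff are blinded, the outcomes are self-reported, and the comparator is a waitlist. Few other protections are available, so the allocation step should be beyond question. A reader of the results could ask whether certain parents were steered towards the app, and the procedure as described gives no ground for ruling it out.

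**Working it through.** The plan gives no figure for concealment, so the check is mainly a comparison of sections. One plan figure is used, the total of 212.

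**1. The plan's sample size.** The inputs from Sample size calculation are 80% power, two-sided 5%, d = 0.5 at T2 reached linearly from T0, AR1 correlation 0.5, and 10% loss at each step (retention 1, 0.9, 0.81). The formula for a linear-trend contrast c = (-1, 0, 1) is n per arm = 2(z₀.₉₇₅ + z₀.₈₀)² × Var / (effect)².
- Var = 1 + 1/0.81 - 2 × 0.5²/√0.81 = 1 + 1.235 - 0.556 = 1.679
- n = 2 × 7.849 × 1.679 / 0.5² = 105.4, rounded up to 106 per arm

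This matches the stated 106 (212 in total). No term depends on who allocates, so the point below leaves the sample size unchanged.

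**2. What the assigning role knows at allocation.**

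| Item | Known to the assigning role? | Section |
|---|---|---|
| Sequence | Yes; made beforehand and joined to IDs | Randomization and treatment allocation |
| Identity behind the ID | Yes; e-mail addresses can be accessed | Data handling, management, and storage |
| Screening result | Yes, in so far as this role reports it to parents | Data handling, management, and storage |
| T0 answers | Not stated | none |

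The word central does not change the picture, because the central person is the investigator.

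**3. Which routes to bias are closed.**
- Selective enrolment: parents register themselves, so nobody on the team is described as choosing whom to enrol next.
- Selective eligibility: exclusion for anxiety or depression is a score of at least 15 on the GAD-7 or PHQ-9 (Participants), collected by online questionnaire.
- Withdrawal on learning the arm, before any data exist: consent and T0 come first, and the analysis is by intention to treat (Statistical analysis).

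**4. Which route stays open.** Allocation takes place after a week's T0 completers have accumulated. The list fixes how many of them go to each arm. Which of them do so depends on the order in which IDs meet the list, and the article states no order.

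Batch size: recruitment is expected to run from September 2024 to January 2025. The exact dates are not given, so I assume between 13 weeks (end of September to start of January) and 22 weeks (start of September to end of January).
- 212 / 22 = 9.6 per week
- 212 / 13 = 16.3 per week

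For illustration, take a batch of 12 filling three complete blocks, with 6 places in each arm. If the order is open, the number of ways to fill the 6 app places is 12! / (6! × 6!) = 924. If the order is fixed beforehand, there is one. This shows the latitude that the procedure leaves. It does not measure bias, which would depend on conduct that no document can show.

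**The case against.** **Operational detail in a condensed article.** The order of ID matching and the custody of the list are often left to the full protocol, and ID order may well be the rule in practice. That is fair, and silence on order alone would not be a finding. What stands is the stated part: the article itself gives the assigning task and the access to identities to one role. A fuller document could add a safeguard, but the arrangement as published has none.

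**Little room to exploit it.** This also stands. Self-enrolment, numeric cut-offs and randomization after T0 close the usual routes.

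Three stronger readings are tempting, and the documents support none of them.

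- *A fixed block of 4 makes allocations foreseeable in general.* The arithmetic is correct for someone who sees past allocations but not the list. Of the six possible blocks, two fix the last two places and four fix the last one, so (2 × 2 + 4 × 1) / 6 = 1.33 of 4 places (33.3%) are certain. The best guess succeeds (1/2 + 2/3 + 2/3 + 1) / 4 = 70.8% of the time. To use this, such a person must also steer the next enrolment, and no such person is described. For someone who holds the list, foreknowledge is complete at any block size. Blocks of 6 or 8 lower the best guess only to 68.3% or 66.6%, so varying the block size would not address the problem.
- *The investigator decides who is eligible.* The article says that this role informs parents about screening. It describes no discretionary judgement of eligibility.
- *Allocation ignores language, and this biases the comparison.* There are four language versions, and "Measures that were not available for a certain language were translated by native speakers". But the article is silent on stratification, and the plural in schemes and lists leaves open whether there is one list or several. If allocation is unstratified, imbalance arises by chance and does not by itself bias the comparison. In simulations of 212 participants in blocks of 4, some language fell outside a 40:60 split in 29% of trials with four equal languages and in 50% with shares of 50/25/15/10%. Those shares are assumed, because the article gives none. The baseline score in the model should absorb part of any difference in level.

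**Conclusion.** The point holds in a limited form. As published, allocation is not concealed from the person who assigns it, because that role applies the pre-made list and can identify the participants. The remaining exposure is the matching of IDs to list slots within a weekly batch, about 10 to 16 people on the assumed recruitment calendar. Its effect on the treatment estimate cannot be quantified and may be nil; nothing suggests that anyone would misuse it.

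The conclusion assumes that no separation of roles or fixed ID order is laid down in a document not shown here. If one is, citing it settles the matter. The change is still worth making because it costs very little before recruitment, whereas doubt about concealment cannot be removed afterwards.

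**What to change.** In Randomization and treatment allocation:

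1. State that each week's IDs are placed in order of T0 completion time stamp before the list is applied, and that list slots are used strictly in sequence. Qualtrics collects the data online, so the time stamps should already exist. Anyone can later compare the time-stamp order with the list.
2. Have an existing team member without participant contact hold the list and allocate, or let the survey system do so. The principal investigator can go on sending invitations and then receives only the resulting assignment.

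The cost is reassigning one task, or some set-up work if the survey system allocates. Nothing changes in sample size, outcomes or visit schedule. The change should be in place before recruitment opens, planned for September 2024. If batches have already been allocated, apply it to the remaining ones and report how IDs were matched in the earlier ones.

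Optionally, add language version as a fixed effect to the linear mixed model in Statistical analysis, which names time, group, their interaction and the baseline score but no language term. With four versions this costs three parameters. It is a gain in precision, separate from the concealment point.

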### Intervention

The Adappt intervention is based on positive psychology and mindfulness and was developed in cocreation with the target group and relevant key stakeholders including professionals working with children with a NDD and their parents (e.g., life-course supporters, social psychiatric nurse, school care coordinator, clinical psychiatrist and teacher at school for children with a NDD) in order to maximize fit of content and increase acceptance. The self-help app consists of a variety of positive psychology and some mindfulness-based exercises. The exercises are based on proven to be effective positive psychology interventions, and the intervention is structured around six themes with five exercises each (see Table 1). Participants will be guided through the intervention by receiving one exercise a day of a theme of choice. Several persuasive technology elements are included in the app to improve adherence to intervention [46], such as guiding participants through the application (tunnelling), and notifications to remind the participant of practicing. The app has been developed by LearnEnjoy (https://learnenjoy.com), a French company specialized in the development of digital interventions for people with and without a NDD.

**Table 1 Tab1:** Overview of positive psychology themes

Theme	Description	Examples of exercises
Strength-based empowerment	Learning and applying your own strengths	Using strengths [58]
Points of light	Attention for the nice small things can be helpful	Three good things [63]
Attention for yourself	Taking care of yourself	Best possible self [61]
Improved connectedness	Improve relationships through attention and gratitude	Acts of kindness [21]
Accept & Let go	Change what you can change, accept what you cannot change and wisdom to see the difference	Cognitive defusion [3]
Asking & Getting help	Ask, refuse, and accept help	Gratitude diary [45]

### Waitlist control condition

Participants in the waitlist control group can start the self-help app after completing the first follow-up questionnaire, 4 months after baseline. The decision for a waitlist control has been made for ethical reasons, since these participants indicated a need for support by signing up for the intervention and we considered it not appropriate to withhold these participants from support for a longer period. With this design, the control group no longer serves as a control after the first follow-up questionnaire (4 months after baseline), since the participants may have then also started to use the self-help app.

### Outcome measures

All study measurements will take place online via the online survey program Qualtrics (https://www.qualtrics.com). An overview of the outcome measures and measurement points can be found in Table 2. Measures that were not available for a certain language were translated by native speakers with back-and-forth translation.

**Table 2 Tab2:** Overview of outcome measures and measurement points

Questionnaire	Number of items	Outcome measure	Screening	T0 (baseline)	T1 (Post-intervention)	T2 (follow-up 1)	T3 (follow-up 2)
GSAAS	10	Ability to Adapt		X	X	X	X
MHC-SF	14	Mental well-being	X	X	X	X	X
PSS	10	Parenting stress		X	X	X	X
HADS-A	7	Anxiety symptoms	X	X	X	X	X
PHQ-9	9	Depressive symptoms	X	X	X	X	X
CAPES-DD	24	Parenting self-efficacy and behavior of the child		X	X	X	X
PAC	9	Positive aspects of caregiving		X	X	X	X
SBI	8	Savoring		X	X	X	X
FSCRS-SF	5	Self-reassuring		X	X	X	X
AAQ-II	7	Psychological flexibility		X	X	X	X
CERQ	16	Positive coping skills		X	X	X	X
MAAS	15	Mindfulness		X	X	X	X
Characteristics		Parental and child characteristics	X^d^	X^d^			
CSQ-8		Client satisfaction			EXP		WL

*EXP* Experimental condition, *WL* Waitlist condition

^a^5 weeks after baseline

^b^4 months after baseline

^c^7 months after baseline

^d^The majority of the characteristics are asked at T0; however, those relevant for inclusion are asked in the screenings questionnaire

#### Primary outcome measure

The primary outcome, ability to adapt will be measured with the 10-item Generic Sense of Ability to Adapt Scale (GSAAS; [32]). Items will be answered on a 5-point scale ranging from not at all (0) to always (4). An average score will be calculated, with a higher score being indicative of higher perceived ability to adapt. Psychometric properties of the GSAAS were found to be good [32].

#### Secondary outcome measures

##### Mental health-related outcomes

Mental well-being will be measured with the 14-item Mental Health Continuum – Short Form (MHC-SF; [47]) with three subscales: emotional (3 items), social (5 items), and psychological (6 items) well-being. Items will be scored on a 6-point scale ranging from never (0) to every day (5). Averages will be calculated for the total mental well-being scale and the three subscales, with higher scores being indicative for more mental, emotional, social, and psychological well-being. Psychometric properties were found to be good [52].

Perceived stress will be measured with the 10-item perceived stress scale (PSS; [17]). Items will be scored on a 5-point scale ranging from never (0) to very often (4). Sum scores will be calculated (0–40), with higher scores being indicative for larger levels of perceived stress. Psychometric properties have been found to be acceptable [54].

Anxiety symptoms will be measured with the 7-item Anxiety subscale of the Hospital Anxiety and Depression Scale (HADS-A; [77]). Items will be scored on a 4-point scale ranging from most of the time (3) to not at all (0). Sum scores will be calculated (0–21), that can be interpreted as no symptoms of anxiety (0–7), possibly an anxiety disorder (8–10), and likely an anxiety disorder (11–21) [42]. Psychometric properties were found to be good [6].

Depressive symptoms will be measured with the 9-item Patient Health Questionnaire (PHQ-9; [49]). A 4-point scale ranging from not at all (0) to nearly every day (3) will be used to score items. Sum scores will be calculated (0–27), that can be interpreted as mild (5–9), moderate (10–14), moderately severe (15–19), and severe (20–27). Psychometric properties were found to be good [49].

##### Parental experiences

Parental self-efficacy (16 items), behavioral (10 items), emotional (3 items), and total (16) problems of the child and prosocial behavior (8 items) of the child will be measured with the 24 item Child Adjustment and Parent Efficacy Scale – Developmental Disability (CAPES-DD; [27]). Parents rate their confidence in managing behavior of the child on a 10 point scale, ranging from “certain I cannot manage” (1) to “certain I can manage it” (10), resulting in a sum score between 16 and 160, with higher scores being indicative of higher parental self-efficacy levels. Child behavior items will be scored on a 4-point scale from not at all (0) to very much (3). Sum scores will be calculated for the subscales emotional problems (0–9), behavioral problems (0–30), prosocial behavior (0–24), and total problems (0–48). Psychometric properties were found to be very good [27].

Positive aspects of caregiving will be measured with the 9-item Positive Aspects of Caregiving (PAC; [68]). Items will be scored on a 5-point scale ranging from disagree a lot (1) to agree a lot (5). A sum score will be calculated (9–45), with higher scores being indicative of more positive aspects of caregiving. Psychometric properties were evaluated and found to be good [68].

